## Abstract

**Background:**

Robot-assisted laparoscopic radical prostatectomy and robot-assisted radical cystectomy have gradually become the preferred choices for urologists as they allow surgeons to perform complex procedures more precisely and effectively. The pneumoperitoneum, which is normally applied in these surgeries to provide visual clarity and space to perform the procedure, may cause hemodynamic disturbance, potentially myocardial injury. Thus surgeons have recently considered opting for the low-pressure pneumoperitoneum to lower this negative impact.

Herein we describe a protocol for a clinical trial to compare the impact of prolonged low-pressure and standard-pressure pneumoperitoneum on myocardial injury after robot-assisted surgery.

**Methods/design:**

This study is designed to be a bicenter clinical trial. In total 280 patients scheduled to undergo robot-assisted laparoscopic radical prostatectomy or robot-assisted radical cystectomy will be enrolled and randomized into two groups, with standard- (12–16 mmHg) and low-pressure (7–10 mmHg) pneumoperitoneum, respectively. Troponin T will be measured as the primary endpoint to assess the extent of myocardial injury. Nt-proBNP and hemodynamic indexes will also be recorded for further analysis.

**Discussion:**

The significance of this study is emphasized by the fact that there are few studies that have focused on the impact of prolonged pneumoperitoneum on myocardial injury, which is relevant to postoperative mortality. We hope that the conclusions drawn from this study could provide reference and basis to the future of the pneumoperitoneum in clinical practice.

**Trial registration:**

Registered at https://www.clinicaltrials.gov with the Identifier NCT02600481 on November 5, 2015

**Electronic supplementary material:**

The online version of this article (doi:10.1186/s13063-016-1609-5) contains supplementary material, which is available to authorized users.

## Background

Robot-assisted surgery allows doctors to perform complex procedures with more precision, flexibility and control. As two major applications, robot-assisted laparoscopic radical prostatectomy (RALRP) and robot-assisted radical cystectomy (RARC) were firstly reported in 2000 [1–3] and 2003 [4], respectively. These procedures are rapidly gaining acceptance among urologists, as the robotic device offers the advantage of the minimally invasive laparoscopic approach but shortens the surgical learning curve [5, 6]. RALRP is now a choice of surgical treatment in most centers of excellence in the USA as well as in other parts of the world, which benefit from its superior visualization and magnification with respect to perioperative parameters [7]. In 2009, over 60,000 cases of RALRP were performed globally, accounting for 70 % of the total number of radical prostatectomies [8]. For RARC, its proportion in the USA increased from 0.6 % in 2004 to 12.8 % in 2010 [9, 10].

Standard-pressure pneumoperitoneum (SPP) is usually achieved by insufflating the abdominal cavity with CO_2,_ and an intra-abdominal pressure (IAP) of 12 to 16 mmHg is considered to be appropriate. SPP usually changes the IAP and systemic hemodynamics [11] causing oxidative [12], ischemia and reperfusion injury in various tissues [13]. Cardiac, pulmonary, intestinal [14], renal [15] and testicular [16] damage caused by SPP have been reported previously. When CO_2_ pneumoperitoneum is performed, the absorption of CO_2_ may lead to arrhythmias, mild acidemia and even severe acidemia; mean blood pressure, heart rate and pulmonary vascular resistance can also be increased [17]. RALRP and RARC are usually performed in the Trendelenburg position, with the patient positioned head-down at a specific angle (normally 15–30°). SSP in the Trendelenburg position causes a drop in left ventricular end-diastolic volume as measured by transthoracic echocardiography; it also affects diastolic function with a delay in deceleration time and isovolumetric relaxation time [18]. The pressure changes caused by pneumoperitoneum can decrease venous return, and subsequently affect cardiac output [19, 20]. All these hemodynamic disturbances may cause prolonged cardiac overload as well as myocardial oxygen imbalance, as the robot-assisted urological surgery usually lasts more than 3 h. Therefore, the potential myocardial injury thus caused is worth investigating.

To lower the impact of pneumoperitoneum on myocardial physiological status while providing appropriate space for operation, low-pressure pneumoperitoneum (LPP) at a range of 7–10 mmHg is considered optimum by surgeons. Numerous clinical trials have been done to compare LPP with SPP in laparoscopic cholecystectomy, the duration of which is often under 2 h [21]. A high IAP pneumoperitoneum was found to be associated with more fluctuations in hemodynamic parameters and increased peritoneal absorption of CO_2_ as compared to LPP in laparoscopic cholecystectomy [22]. Cardiac electrophysiological analysis showed that LPP results in lower sympathetic activation than SPP [23]. Prolongation of corrected QT dispersion (QTcd), which is associated with cardiovascular morbidity and mortality, was significantly higher in the high-pressure pneumoperitoneum group (15 mmHg) than in the LPP group (7 mmHg) [24]. In addition, a study focusing on solid intra-abdominal-organ flow suggested that increased intraperitoneal pressure substantially reduced the portal venous flow as compared with lower IAP [25]. A randomized controlled trial conducted by Kanwer et al. showed that LPP used in laparoscopic cholecystectomy benefited patients by lowering postoperative pain intensity [25, 26]. Hua et al. performed a meta-analysis in 2013 and showed that LPP was feasible and safe, resulted in reduced postoperative pain and nearly the same operative time as SPP [26, 27]. Prolonged robot-assisted surgery normally takes 4–5 h, sometimes 7–8 h, which is much longer than the time taken for cholecystectomy. Thus the outcome might be different, due to the different lengths of surgical time. So far, there are few studies concerning the comparison of LPP and SPP on myocardial injury after prolonged robot-assisted urological surgery. Postoperative myocardial injury after noncardiac surgery (MINS) has been proved to be an independent predictor of 30-day mortality [28]. An elevated troponin T (TnT) level after noncardiac surgery, irrespective of the presence of an ischemic feature, independently predicted 30-day mortality. A peak TnT level of 0.03 ng/mL or greater was used as diagnostic criterion for MINS in a cohort study reported in 2014 [29]. The N-terminal of the prohormone brain natriuretic peptide (Nt-proBNP) is an indicator for cardiac failure and is being used in routine tests in the emergency room [30]. It has been demonstrated that peak Nt-proBNP levels at peak IAP were correlated positively with indexes of cardiac afterload (systemic vascular resistance (SVR) and peripheral vascular resistance (PVR)). A strongly negative correlation between Nt-proBNP levels and cardiac output at peak IAP was also reported [31].

The present study was designed to compare the effects of prolonged LPP and SPP on myocardial injury after a relatively long period of surgery. The TnT level is chosen as a primary endpoint for the evaluation of myocardial injury as it has been shown to be a sensitive predictor of cardiac injury. Our working hypothesis is that LPP can result in improved myocardial outcome after robot-assisted urological surgery.

## Methods/design

### Study design

This study is a prospective, bicenter, single-blinded, randomized controlled clinical trial to investigate the different effects of prolonged LPP and SPP on myocardial injury after RALRP and RARC (Fig. 1).

**Fig. 1 Fig1:**
[figure not shown]
Study design and participant flow chart. *RALRP* robot-assisted laparoscopic radical prostatectomy, *RARC* robot-assisted radical cystectomy

### Study population

Patients who are scheduled to undergo long-duration RALRP or RARC in the Huadong Hospital Affiliated to Fudan University and the Ruijin Hospital Shanghai Jiao Tong University School of Medicine, in line with the inclusion criteria, will be recruited. From the previous data and estimation, the annual number of patients meeting the criteria is over 170.

Inclusion criteria:Scheduled to undergo RALRP or RARC, with an estimated duration of over 3 hAmerican Society of Anesthesiologists’ (ASA) classification of I or IIAge is between 18 and 80 yearsPreoperative troponin T level is normal

Exclusion criteria:Patients with preoperative cardiopulmonary dysfunction who cannot undergo prolonged surgeries in the Trendelenburg position and/or those with severe pulmonary dysfunction with a New York Heart Association (NYHA) classification of III–IVBody Mass Index >30 and weight <18 kgAny intraoperative situation as follows: (1) any cause to cancel the operation or change robot-assisted urological surgery to open surgery, (2) intraoperative cardiovascular accidents

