Other rare complications of pneumoperitoneum include pneumothorax, inadvertent gas embolism, vascular injury and inadvertent extraperitoneal insufflation.

As described above, the pneumoperitoneal physiology in the Trendelenburg position is intricate. We aim to protect the patients from injury by careful preoperative examination, so that undiagnosed conditions can be identified and pretreated. Standard intraoperative monitoring will be used for all patients, and invasive hemodynamic monitoring (Vigileo with the FloTrac system) will be used to monitor the cardiovascular response to pneumoperitoneum and position changes. ETCO_2_ and airway pressure are commonly assessed to assure adequacy of ventilation and blood gas analysis will be conducted when necessary. Other rare complications will be appropriately treated as soon as they are detected.

Data attrition of the clinical trial would affect the validity of our results markedly. In this study, approaches will be adopted to minimize any impact this may bring. The designed follow-up period of this study is only 24 h post surgery, so it is unlikely that the patients who meet the inclusion criteria would drop out, which is confirmed by the ongoing preliminary trial. Besides, we have the capability for a rapid response to any perioperative emergency events. If attrition does occur, we will carefully discuss the reasons and estimate the impact on the trial. If it is not a source of bias we will employ the complete-case method, where the missing data will be excluded from the analysis. As we have a population large enough to complete the trial in the designated period, this is believed to be the simplest and most efficient method for our study.

The main limitation of this trial is the inevitable bias in age and sex distribution of the enrolled patients. Although the age range in the inclusion criteria is set at 18–80 years, most patients requiring urological surgery, especially resection, are middle-aged and elderly men. Thus the conclusion drawn by this study might be not applicable to female patients and cases in different age groups.

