As the trial designed in this study is bicenter, the bias caused by the differences in execution between centers and patient preference of hospital selection might be a challenge. Both the hospitals participating in this trial are tertiary referral centers in Shanghai, but located over 20 km apart and there is an existing long-term collaboration between the two hospitals, which is the basis of this study. From the past years’ patient baseline data, there is no significant competitive recruitment or imbalance between the two hospitals. Thus it could be supposed that the potential bias of those enrolled would not markedly affect the outcome of this study. However, to eliminate any bias caused by variability in anesthesiologists’ abilities, regular meetings and training for clinicians participating in this clinical trial will be ongoing and continued into the future.

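### The body-size exclusion cannot work as written: BMI above 30 joined by *and* to a weight below 18 kg is unusable in adults on either reading

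*Protocol article*

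**What the plan says.** The Study population section of the Protocol article admits patients aged 18 to 80 years, of ASA class I or II, who are scheduled for robot-assisted prostatectomy or cystectomy expected to last more than 3 hours. One exclusion item is the body-size rule: "Mass Index >30 and weight <18", the second limit being given in kilograms. No other section restates or corrects it. The Discussion expects that most patients needing urological surgery, "especially resection, are middle-aged and elderly men".

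The item before it has two limbs joined by *and/or*. The first is general: "Patients with preoperative cardiopulmonary dysfunction who cannot undergo prolonged surgeries in the Trendelenburg position". The second concerns "severe pulmonary dysfunction with a New York Heart Association (NYHA) classification of" III–IV.

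Patients are recruited at two hospitals, 140 at each (Sample size calculation). The surgeon registers each patient after a clinical evaluation (Randomization and blinding). The Discussion names "the bias caused by the differences in execution between centers" as a possible challenge.

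**The concern.** An eligibility rule should sort patients the same way whoever applies it. This one joins an upper limit on BMI to a very low limit on body weight. The two describe opposite extremes of body size, and 18 kg is not a usable weight limit for adults. A clinician at either hospital has to guess what was meant. One site might exclude everyone with BMI above 30. The other might follow the literal text and exclude nobody for body size.

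At stake are who is enrolled, whether both centres enrol on the same terms, and whether a reader can tell which population the results describe. The trial already treats variation between centres as a concern and plans a homogeneity assessment across hospitals (Statistical analysis). Ambiguous eligibility text is an avoidable source of such variation.

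**Working it through.** No sample size, power or alpha figure in the plan depends on this rule, so there is no stated figure to reproduce. The check is whether any adult can meet the rule.

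**Inputs** (Study population): BMI > 30; weight < 18 kg; age 18 to 80 years. The heights below are illustrative adult values, not taken from the document.

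**Reading 1: both conditions must hold.** BMI = weight / height², with weight in kg and height in m.

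- BMI > 30 means height² < weight / 30.
- With weight < 18 kg, height² < 18 / 30 = 0.60.
- So height < √0.60 = 0.775 m.

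No realistic adult surgical patient is that short, so the rule excludes no one.

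**Reading 2: each condition is a separate exclusion.** Each limit is set against ordinary adult heights:

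| Height (m) | BMI at 18 kg = 18/h² | Weight at BMI 30 = 30h² (kg) |
|---|---|---|
| 1.50 | 8.0 | 67.5 |
| 1.60 | 7.0 | 76.8 |
| 1.70 | 6.2 | 86.7 |
| 1.80 | 5.6 | 97.2 |

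The BMI limit falls at ordinary adult weights and does exclude patients. The weight limit corresponds to a BMI of 5.6 to 8.0 and excludes no realistic adult.

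**What the number 18 may have been.** If 18 were a BMI, the corresponding weights (18h²) would be 40.5, 46.1, 52.0 and 58.3 kg at the same four heights, which could apply to adults. The line therefore reads like an upper and a lower BMI limit with the wrong variable and unit. The document does not say so, and this remains a conjecture for the sponsor to confirm. A lost *per square metre* alone would not explain the line: the variable named is weight, and a BMI cannot be both above 30 and below 18, so *and* would still fail as a conjunction.

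**Side note: the NYHA clause.** The clause names the lung but grades severity with New York Heart Association class, a cardiac functional class. Organ and scale do not match. The first limb of the same item covers heart and lung together and needs no scale, and the ASA I or II requirement probably screens out many of the same patients.

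**The case against.** The strongest objection is that *and* in a list of exclusions often just lists two excluded groups. On that reading patients with BMI above 30 are excluded, and the only fault is a weight limit that nobody reaches. This stands in part. The statement that the rule excludes nobody holds only on the literal conjunction. It does not rescue the line, because half of it remains empty on either reading and nothing in the article says which reading applies.

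A second objection is that this is a drafting slip, that the full protocol may carry the right wording, and that neither hospital is shown to read the line differently. The full protocol is indeed not available. However, the article printed the criterion rather than leaving it out, and printed it wrongly. Divergence between sites is a possibility, not an observed fact.

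Three stronger inferences are tempting but unsupported:

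- **A count of wrongly enrolled patients.** The article gives no BMI distribution, and any count would also need literal application at both sites.
- **That the faulty rule exposes patients to surgery they should not have.** Recruits are already scheduled for the operation. The rule governs trial entry only, and no reason for the BMI limit is given.
- **That the treatment comparison is biased.** Patients are randomised after eligibility is judged, so ambiguity at entry bears on both arms alike.

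The NYHA mismatch is real, but as loose wording within a criterion whose first limb still works. It does not carry the point.

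**Conclusion.** The point holds as a specific error in an operative eligibility criterion. On the literal reading the body-size rule excludes no realistic patient, since it needs a height below 0.775 m. On the listing reading its weight half excludes no realistic adult. The only assumption is that enrolled adults have ordinary adult heights and weights.

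The consequence is limited to case mix, consistency between the two centres and generalisability. How many enrolments would change cannot be estimated from the document. The low-pressure versus standard-pressure contrast stays protected by randomisation, and the 280 patients and the stated power are unaffected. The line should be corrected because it is wrong and cheap to repair, not because it threatens the main result. The NYHA wording is a minor matter to tidy at the same time.

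**What to change.** Before the first patient is enrolled, the sponsor should state which body-size limits were intended. The line should then be rewritten as alternatives joined by *or*, each with its correct variable and unit. If an upper and a lower BMI limit were meant, both should be given in kg/m²; that is for the sponsor to confirm. Both hospitals should use the identical text.

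In the same edit, the wording that grades severe pulmonary dysfunction by NYHA class should be reconciled, so that the organ named and the scale used match. How to do so is for the sponsor to decide.

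The cost is a few words. Trial status says inclusion has not started, so no enrolled patient would be affected. The one downside is that the eligible pool will be smaller than under the literal text, by an amount the document does not allow one to calculate.

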### Study group

This study will consist of two arms, the low-pressure pneumoperitoneum group (LP) and the standard-pressure pneumoperitoneum group (SP). The estimated number of patients hospitalized for prolonged robot-assisted urological surgery is 140 in each group. The IAP for the LP group will be held at 7–10 mmHg, while it will be held at 12–16 mmHg for the SP group, both insufflated at low speed (2 L/min), during the robot-assisted urological surgery. The CO_2_ pneumoperitoneum will be administrated using automatic insufflators (Karl Storz, Tuttlingen, Germany).

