### Randomization and blinding

Patients will be recruited in two hospitals: Huadong Hospital Affiliated to Fudan University and Ruijin Hospital Shanghai Jiao Tong University School of Medicine. Patients who meet the eligibility criteria will be randomly assigned to the two treatment groups: SP or LP. The randomization plans will be implemented using statistical software R, and will be stored in an online database. After a clinical evaluation, the surgeon will register the patient using a unique ID assigned to the patient and used to select a random assignment from the database. The physicians will be aware of the group to which the patients are allocated while the patients will not.

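### Conversion to open surgery and intraoperative cardiovascular accidents are exclusion criteria although they follow randomisation, so applying the rule breaks the randomised comparison

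*Protocol article*

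**What the plan says.** Under Study population, the Protocol article lists intraoperative situations as exclusion criteria beside the preoperative ones: "1) any cause to cancel the operation or change robot-assisted urological surgery to open surgery, (2) intraoperative cardiovascular accidents".

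Under Randomization and blinding, "Patients who meet the eligibility criteria will be randomly assigned to the two treatment groups: SP or LP". On timing it says: "After a clinical evaluation, the surgeon will register the patient using a unique ID assigned to the patient and used to select a random assignment". On blinding: "The physicians will be aware of the group to which the patients are allocated while the patients will not".

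Under Study group, "The IAP for the LP group will be held at 7–10 mmHg, while it will be held at 12–16 mmHg for the SP group", during the operation.

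The Abstract says that pneumoperitoneum "may cause hemodynamic disturbance, potentially myocardial injury". The Background adds that CO2 absorption "may lead to arrhythmias, mild acidemia and even severe acidemia". The Abstract also gives the purpose of the pneumoperitoneum as view and working space.

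On attrition, the Discussion says: "If it is not a source of bias we will employ the complete-case method, where the missing data will be excluded from the analysis". No section states that patients with an intraoperative exclusion stay in the analysis.

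**The concern.** An exclusion criterion should be a fact known before assignment. Conversion and intraoperative accidents become known only during surgery, when the assigned pressure is already acting. If either depends on the arm, the patients left in the two groups are no longer comparable, whatever the quality of the randomisation.

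The cardiovascular item is the more serious. The trial asks whether lower pressure reduces myocardial injury, and the rule would remove patients whose injury, or the disturbance leading to it, shows itself on the table. The protocol's own rationale would place more of them in the standard-pressure (SP) arm, so the rule would hide part of the effect sought. Conversion could act the other way: if a restricted view at low pressure (LP) led to more conversions, the hard cases would leave the LP arm and flatter it. Physicians who know the allocation attend the operation, where conversion is decided and an event is recognised as an accident, so knowledge of the arm can also influence who is excluded.

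**Working it through.** **Order of events.** Assignment is drawn at registration after a clinical evaluation (Randomization and blinding). The pressure range defines the arm and is held during surgery (Study group), so the arm must be known before insufflation. Any conversion or accident under pneumoperitoneum therefore follows assignment. A cancellation before insufflation is the one listed event that the pressure cannot cause.

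**The plan's own figure.** Sample size calculation gives power of at least 0.70 with 140 per arm for an 80% increment in patients with troponin T (TnT) of 0.02 or higher. Base rate, alpha and sidedness are not stated. I assume a relative increase and two-sided alpha 0.05. Write d for the difference, s0 for the pooled standard error and s1 for the unpooled one:

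power = Φ((d − 1.96·s0)/s1)

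At 15% (LP) and 1.8 × 15% = 27% (SP): d = 0.120, s0 = 0.0487, s1 = 0.0482, power = 0.695. So 15% versus 27% is a scenario consistent with the stated 0.70.

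**Scenario A: a true effect, with exclusions from SP only (assumed).** The expected number of SP positives is 0.27 × 140 = 37.8. After dropping k positive patients, the SP rate is (37.8 − k)/(140 − k). LP stays at 15% of 140.

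| k dropped | SP rate | difference (points) | power |
|---|---|---|---|
| 0 | 27.0% | 12.0 | 0.70 |
| 1 | 26.5% | 11.5 | 0.66 |
| 2 | 25.9% | 10.9 | 0.62 |
| 3 | 25.4% | 10.4 | 0.58 |
| 5 | 24.3% | 9.3 | 0.49 |

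**Scenario B: no true effect, with conversions more frequent in LP (assumed).** Both arms have a true rate of 15%. If a share e of an arm is excluded and a proportion q of those are TnT-positive, the rate among the retained is (0.15 − e·q)/(1 − e). The last column is the chance of a significant result favouring LP.

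| converted LP / SP | q | LP rate | SP rate | false result for LP |
|---|---|---|---|---|
| none | – | 15.0% | 15.0% | 0.025 |
| 3% / 1% | 0.3 | 14.5% | 14.9% | 0.030 |
| 3% / 1% | 0.5 | 13.9% | 14.6% | 0.037 |
| 8% / 0% | 0.5 | 12.0% | 15.0% | 0.108 |

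For the last row: (0.15 − 0.08 × 0.5)/0.92 = 0.1196, d = 0.0304, s0 = 0.0418, s1 = 0.0416, and Φ((0.0304 − 1.96 × 0.0418)/0.0416) = 0.108.

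**Sensitivity to the test.** The Statistical analysis section names Fisher's exact test. Computed exactly, the extreme case of A goes from 0.65 to 0.46 and that of B from 0.017 to 0.090. The levels are lower, but the direction and rough size of the shift are the same.

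**The case against.** The moment of randomisation is not printed and the flow chart is not shown. The order of events is therefore an inference, although a strong one.

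A reader might infer that the most injured patients will in fact be removed, and at different rates by arm. The document does not show this. For cardiovascular accidents it is a plausible consequence of the stated rationale. For conversion, no section links low pressure to conversion, or conversion to raised TnT. The Background even cites a meta-analysis finding low pressure feasible and safe with similar operating time, although the Background sets that evidence in cholecystectomy, a much shorter operation. Patients are ASA I–II with normal preoperative TnT, so accidents may be few, and the largest figures above are worst cases. If exclusions were few, balanced and unrelated to TnT, the bias would be negligible.

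A reader might also infer that sampling stops after conversion or an accident, so that the data are lost for good. The document does not say so. Nor does the complete-case sentence say that a patient who misses one of the four draws is removed altogether. The Discussion also promises to examine reasons for attrition and estimate their impact. That passage concerns drop-out, though, not patients the protocol itself excludes.

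Finally, an analysis plan that is not shown may define an intention-to-treat set. It would then contradict the criterion printed here, so the two would still have to be reconciled.

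**Conclusion.** The point holds as a defect in a stated rule, not as a missing detail. Two of the listed exclusions, conversion and intraoperative cardiovascular accident, can arise after assignment. One is on the pathway the trial studies, the other may depend on pressure, and nothing printed keeps these patients in the comparison. The possible bias runs in either direction, so it cannot be discounted as conservative.

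Its size is unknown because the protocol gives no event, conversion or base rates. Under the assumed 15% versus 27%, one to five one-sided exclusions cost between 0.04 and 0.20 of power (0.70 to 0.66, and 0.70 to 0.49 before rounding differences). Under no effect, the chance of falsely favouring low pressure ranges from about 0.03 to 0.04 with modest imbalance, up to 0.11 in the worst case. Confidence is high that the defect exists and low on how large it would be. It should be corrected before enrolment, which had not begun according to Trial status.

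**What to change.** - Limit the exclusion criteria to facts known before randomisation, and move conversion and intraoperative cardiovascular accidents out of the list.
- Draw TnT at Ta to Td in every randomised patient whose operation starts, converted or not, and analyse by assigned group.
- Report conversions and intraoperative cardiovascular accidents by arm as outcomes.
- Leave out only operations cancelled before insufflation, and report these by arm.
- Keep the set without these events as a sensitivity analysis.

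The TnT endpoint and the planned tests can stay as they are. The cost is protocol wording, a few extra blood draws within the existing 24-hour follow-up, and slight dilution of the effect by converted patients.
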